## **1.7 Study Rationale**

This study will evaluate using the combination of Daratumumab (Darzalex) with carfilzomib (Kyprolis), lenalidomide (Revlimid), and dexamethasone (D-KRd) as initial treatment for subjects diagnosed with

MM. The proposed strategy is based on the following rationale: (1) The results indicate that the KRd combination (formerly CRd) is highly active in newly diagnosed multiple myeloma (NDMM). In the initial study of KRd treatment of NDMM patients of all ages with protocol-recommended delayed transplant for transplant candidates, best response for all patients on ITT (N=53) was 98% PR, 87% VGPR, 72% >nCR, 64% CR, 55% sCR, and 51% MRD-negative rate, 4-year PFS of 69%. In a more recent and ongoing study of the treatment of transplant candidates with NDMM with KRd pre- and post-autologous stem cell transplant (KRd+ASCT), candidates with 4 KRd cycles before ASCT followed by 4 cycles of KRd consolidation, followed by 10 cycles of KRd maintenance, an addition of transplant appeared to provide statistically higher rates of sCR at the end of 8 cycles (69% vs 30% for KRd+ASCT vs KRd without ASCT) and overall higher rates of sCR, reaching over 80% at the end of KRd treatment and high rates of MRD-negative disease, which are exceeding 70% by either multi-color flow cytometry (MFC) or by next gene sequencing (NGS) at the end of extended total 18 cycles of KRd treatment. The extended treatment overall was well tolerated, with comparable toxicity rates between these two studies, and low rates of discontinuation due to toxicities (<5%), and no treatment-related death, which corroborates with observations of generally acceptable safety profile of KRd vs Rd based on randomized ASPIRE study results in relapsed myeloma. (2) Combination of daratumumab with lenalidomide and dexamethasone is highly active and well tolerated in relapsed MM based on POLLUX randomized study (D-Rd vs Rd), with response rates among the highest, if not the highest in this patient population (>PR 92.9%, CR rate 43.1%, and MRD-negative rate 22.4%), associated with best-to-date PFS in relapsed myeloma of 85.7% at 12 months, with median not reached at median 13.5 months of follow-up, which performed well in all categories significantly higher than in control Rd arm with PFS superior by hazard ratio 0.37; 95% confidence interval [CI], 0.27 to 0.52; P<0.001 by stratified log-rank test. Toxicities were for most categories not significantly different or only slightly higher in daratumumab arm, mostly related to longer treatment on daratumumab arm, with the exception of higher rates of neutropenia and infusion reaction, although these events did not result in higher rates of discontinuation or death. (3) Similarly, the combination of daratumumab with proteasome inhibitor (bortezomib) and dexamethasone (D-Vd) shows superior activity compared to Vd in randomized CASTOR trial, with PR rate in D-Vd arm 82.9%, and with significantly superior PFS compared to Vd arm (not reached vs 7.2 months; hazard ratio 0.39, 95% confidence interval, 0.28 to 0.53; P<0.001). Other than daratumumab-related infusion reactions, adverse events in daratumumab arm were mostly comparable, except higher rates of neutropenia and thrombocytopenia in daratumumab arm, which did not affect discontinuation rates. While there is no data

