## 5 Patient Selection

### 5.1 Inclusion Criteria

Subjects must meet all of the following inclusion criteria to be eligible to enroll in this study. No enrollment waivers will be granted.

1. Newly diagnosed, previously untreated myeloma requiring systemic chemotherapy
  - Prior treatment of hypercalcemia or spinal cord compression or active and/or aggressively progressing myeloma with corticosteroids or lenalidomide or bortezomib-based regimens does not disqualify the patient (the treatment dose should not exceed the equivalent of 160 mg of dexamethasone in a 4-week period or not more than 1 cycle of PI/IMiD-based therapy).
2. Both transplant and non-transplant candidates are eligible
3. Diagnosis of symptomatic multiple myeloma as per current IMWG uniform criteria prior to initial treatment
4. Monoclonal plasma cells in the BM  $\geq 10\%$  or presence of a biopsy-proven plasmacytoma
5. Measurable disease, prior to initial treatment including any emergent treatment of myeloma. Measurable disease will be indicated by one or more of the following:
  - Serum M-protein  $\geq 1$  g/dL
  - Urine M-protein  $\geq 200$  mg/24 hours
  - If serum protein electrophoresis is felt to be unreliable for routine M-protein measurement, then quantitative immunoglobulin levels are acceptable

- Serum Freelite measurable disease as per current IMWG criteria
6. Bone marrow specimen will be required at study entry; available DNA sample from pre-induction BM will be used for calibration step for MRD evaluation by gene sequencing
  7. Males and females  $\geq 18$  years of age
  8. ECOG performance status of 0-1
  9. Adequate hepatic function, with bilirubin  $\leq 1.5 \times \text{ULN}$  and aspartate aminotransferase (AST) and alanine aminotransferase (ALT)  $\leq 3 \times \text{ULN}$
  10. ANC  $\geq 1.0 \times 10^9/\text{L}$ , hemoglobin  $\geq 8 \text{ g/dL}$ , platelet count  $\geq 75 \times 10^9/\text{L}$
  11. Calculated creatinine clearance (by Cockcroft-Gault)  $\geq 50 \text{ mL/min}$  or serum creatinine below  $2 \text{ g/dL}$
  12. FCBP must have 2 negative pregnancy tests (sensitivity of at least  $50 \text{ mIU/mL}$ ) prior to initiating lenalidomide. The first pregnancy test must be performed within 10-14 days before and the second pregnancy test must be performed within 24 hours before lenalidomide is prescribed for Cycle 1 (prescriptions must be filled within 7 days).

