#### **10.1.2 Secondary Objectives**

Secondary objectives include characterization of efficacy variables:

- Rate of MRD by next generation gene sequencing (NGS) by clonoSEQ (Adaptive Biotechnologies) at the end of Cycle 8 and at the end of cycle 24, and then yearly for as long no PD up to 2 years
- Duration of response (DOR), progression free survival (PFS), time to progression (TTP), and overall survival (OS)
- Overall response rate defined as partial response or better (>PR) including the rate of VGPR or better (>VGPR) and near complete response or better (sCR/CR/nCR) across entire treatment in high risk and low risk patients at indicated time points and as best response.
- Safety and tolerability of combination of D-KRD.

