### **10.2.3 Secondary Endpoint Analysis**

The rate of MRD-negative disease by NGS will be reported at screening, 8, 12, 18, 24 months and then yearly until progression up to 5 years. Additionally, sites will be required to provide unstained pre-treatment slides to assess MRD by Adaptive. Comparison between D+KRd and historical KRd+ASCT rates will be made using a standard chi-square or Fisher's exact test. At the conclusion of the trial, with all subjects evaluated for PFS assessment at 5-years, the rate of MRD-negative status will be compared between D+KRd and historical KRd+ASCT data. This analysis will be conducted by contingency tables, or by adjusted logistic regression models, which will explore for any important confounders. Improvement of response during therapy measured at 6 and 12 months first treatment on protocol will be compared between D+KRd and historical KRd+ASCT data. Proportions of improving patients will be reported by treatment group, and comparisons of those proportions will be conducted using the chi-square or Fisher's exact tests. Overall survival will be calculated from date of first treatment on protocol until death from any cause and measured based upon the intention-to-treat paradigm, and will be compared between D+KRd and historical KRd+ASCT data using Kaplan and Meier survival models and the log-rank test statistic. In addition, all secondary endpoints will be tested for differences to historical controls using the one-sample log-rank test. The duration of MRD-negative disease will be calculated between the date of first occurrence of MRD-negative status, until such time as MRD-positive disease assessment or date of disease progression. Comparisons of duration of MRD-negative status may require the use of interval censoring methods. And finally, safety of the regimens will be assessed by comparing CTCAE Grade toxicity occurrence between D+KRd and historical KRd+ASCT data. Toxicity of Grade 2 and higher will be tabulated for each system organ class (SOC) and common individual toxicities occurring with SOC's reported. The maximum graded toxicity overall and within SOC will be reported per patient with the results summarized by treatment group and frequencies compared using chi-square tests or Fisher's exact tests as appropriate.

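### The one-sample log-rank test is assigned to secondary endpoints it cannot analyse, and the KRd+ASCT comparisons mix regimen with transplant eligibility

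*Protocol*

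**What the plan says.** The secondary objectives in Section 10.1.2 combine several types of outcome. Three are rates or frequencies: "Rate of MRD by next generation gene sequencing (NGS) by clonoSEQ" at set time points, "Overall response rate defined as partial response or better (>PR" with its deeper-response categories, and "Safety and tolerability of combination of D-KRD". One line lists times to event: "Duration of response (DOR), progression free survival (PFS), time to progression (TTP), and overall survival (OS". Section 3.2 adds the correlation between sCR and MRD status.

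Section 10.2.3 then assigns tests. For rates: "Comparison between D+KRd and historical KRd+ASCT rates will be made using a standard chi-square" or Fisher's exact test. The same tests are named for the proportion of patients whose response improves and for toxicity frequencies. OS is compared with KRd+ASCT by Kaplan-Meier curves and the log-rank test. The next sentence, introduced as an addition, says that "all secondary endpoints will be tested for differences to historical controls using the one-sample log-rank test". Adjusted logistic regression appears once, for the MRD-negative rate, as an alternative to contingency tables.

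On populations, Section 1.7 describes the KRd+ASCT source as a "study of the treatment of transplant candidates with NDMM with KRd pre- and post-autologous stem cell transplant (KRd+ASCT". Section 5.1 of this trial says "Both transplant and non-transplant candidates are eligible".

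**The concern.** A one-sample log-rank test compares the observed number of events with the number expected under a reference survival curve. It needs event times and a reference. A proportion at a fixed time, a correlation or an adverse event frequency supplies neither, so for those endpoints the sentence cannot be followed. For OS, where it can be followed, it adds a second p-value to the one already planned. Nothing says which takes precedence, or whether the historical control is KRd+ASCT or KRd without ASCT. The reported result could then depend on a choice made after the data are seen.

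The population issue affects interpretation. Section 1.7 puts forward the hypothesis that D-KRd without transplant may do at least as well as KRd+ASCT, and Section 10.2.2 looks for evidence of similar efficacy. If one side contains only transplant candidates and the other contains both groups, a difference, or the absence of one, may reflect who was eligible for transplant and not the regimen.

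**Working it through.** **Step 1. Endpoint against test.** The protocol gives no alpha, power or sample size for the secondary comparisons, so there is no stated figure to reproduce. The check is on the text of Sections 3.2, 10.1.2 and 10.2.3.

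| Secondary item | Type | Other test named in 10.2.3 | Does a one-sample log-rank apply? |
|---|---|---|---|
| MRD rate at fixed times | proportion | chi-square or Fisher; contingency table or logistic model | no |
| ORR, VGPR or better, nCR or better | proportion | chi-square or Fisher, if the general wording on rates is read to cover them | no |
| sCR-MRD correlation | association | none | no |
| Adverse event frequencies | proportion | chi-square or Fisher | no |
| OS | time to event | two-sample log-rank against KRd+ASCT | yes, but as a second test |
| PFS, TTP, DOR | time to event | none | yes, reference not named |

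**Step 2. Populations.**

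- This trial: 45 patients, transplant and/or non-transplant candidates, with no fixed mix (Section 10.2.1). Only frail non-transplant candidates are excluded (Section 5.2).
- KRd+ASCT: transplant candidates only (Section 1.7). Cohort size not given.
- KRd without ASCT: patients of all ages, with delayed transplant recommended for candidates, N=53 (Section 1.7).

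Nothing in Section 10.2.3 restricts or stratifies the KRd+ASCT comparisons by candidacy. The OS, response-improvement and toxicity comparisons have no adjustment at all.

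**Step 3. Illustration: treating the reference as exact.** Assume the historical curve is estimated from m patients, each carrying the same information as a patient in this trial. The variance of the difference is then proportional to 1/45 + 1/m, while the one-sample test counts only 1/45. The ratio is 1 + 45/m, and a nominal two-sided 5% test has actual size 2 × (1 − Φ(1.96 / √(1 + 45/m))).

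- m = 50: ratio 1.90, 1.96/1.378 = 1.422, size 0.155.
- m = 53: ratio 1.849, 1.96/1.360 = 1.441, size 0.150.
- m = 100: ratio 1.45, 1.96/1.204 = 1.628, size 0.104.

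The 5% level, the range of m and the equal-information condition are assumptions. Only 45 and 53 come from the protocol.

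**Step 4. Illustration: case mix.** Suppose D-KRd matches KRd+ASCT exactly in transplant candidates, non-transplant candidates are a share q of the trial, and their rate is d points lower. The pooled rate is then q × d points too low. With q = 1/3 and d = 20 this is 6.7 points. With q from 20% to 60% and d from 10 to 30 points it runs from 2 to 18 points. Neither q nor d has a source in the protocol, so this shows how the shift arises and is not an estimate of it.

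**The case against.** The strongest reply is that the defect is narrower than it looks. The one-sample test is an addition: chi-square or Fisher tests are already named for rates, response improvement and toxicity, so no listed comparison of rates depends on it. A reader might infer that the rates have no valid test; the text does not support that. The sentence also sits between the OS test and the duration of MRD negativity, so its author may have had only time-to-event endpoints in mind. Sections 3.1 and 10.2.2 even treat time to sCR and to MRD negativity as censored times, so a log-rank on those would be conceivable. All of this stands, but the wording is still "all secondary endpoints will be tested for differences to historical controls using the one-sample log-rank test", and the secondary MRD endpoint is a rate at set time points.

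A reader might also infer that the one-sample log-rank is invalid in itself. It is not: for PFS, TTP, DOR and OS it is a legitimate test, and taking a reference as fixed is a familiar convention. The primary test does the same with its 30%. Nor does the protocol show that the p-values will be too small by any given amount. A historical cohort with longer follow-up and more events per patient would shrink the inflation in Step 3.

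On case mix, excluding frail non-transplant candidates and requiring ECOG 0-1 narrows the gap in fitness. If non-transplant candidates respond less well, the efficacy bias runs against D-KRd, which is conservative for a claim of comparable results. Covariate lists may properly be left to a statistical analysis plan. These points limit the size of the problem. They do not remove it, because the protocol itself sets the comparator and the unadjusted tests for OS, response improvement and toxicity.

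**Conclusion.** The point holds on the text in two parts. First, a test for event times is assigned to every secondary endpoint, including several it cannot analyse, and OS receives two log-rank tests with no priority and no named reference for the second. Second, the KRd+ASCT comparisons of OS, response improvement and toxicity confound regimen with transplant eligibility; only the MRD-negative comparison has an adjusted option.

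The size cannot be computed from the protocol, because neither the KRd+ASCT cohort size nor this trial's case mix is given. The rise from 5% to about 16% to 10% holds only for 50 to 100 historical patients with equal information per patient, and the case-mix shift rests wholly on assumed inputs. None of this touches the primary test. It should be corrected because the comparison with KRd+ASCT is one the protocol intends to interpret.

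**What to change.** In Section 10.2.3:

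- Limit the one-sample log-rank test to PFS, TTP and DOR, name the reference curve for each, and state that its sampling error is ignored. Where patient-level historical data exist, use a two-sample test instead. Simply deleting the sentence would leave these three endpoints with no stated test.
- For OS, name one test: the two-sample log-rank already specified.
- Keep the chi-square or Fisher tests already named for rates and toxicity, and add confidence intervals.
- Make the KRd+ASCT comparisons in this trial's transplant candidates, or stratify them by candidacy, and label them descriptive.
- Compare the whole cohort with the study of KRd without ASCT, whose all-ages population with delayed transplant is closer to this one.

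This changes analysis wording only, with no new data collection in this trial. The price is fewer patients, and so wider intervals, in the KRd+ASCT comparison.

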### **4 INVESTIGATIONAL PLAN**

#### **4.1 Overview of Study Design and Dosing Regimen**

This study will be a multi-center, open-label, phase 2 study, enrolling subjects with newly diagnosed MM requiring systemic chemotherapy. All dosing schedule is based on 28-day cycles. Subjects will receive treatment until disease progression or unacceptable toxicity (whichever occurs first).

Enrolled subjects will initially receive lenalidomide at 25 mg per dose (see below if previously unable to tolerate 25 mg) on Days 1-21. Carfilzomib will be dosed at 20 mg/m^2 on Days 1 and 2 and 36mg/m^2 thereafter (Days 8,9,15, and16). Alternative escalation will be allowed on Cycle 1 if the treating

investigator considers it necessary as follows: 20 mg/m^2 on Days 1 and 2 escalated to 27 mg/m^2 on Days 8 and 9, and then to 36 mg/m^2 on Days 15 and 16. Daratumumab will be administered by subcutaneous injection, provided as a fixed-dosed of 1800 mg and 30,000 units hyaluronidase per 15 mL (120 mg and 2,000 units/mL) for all cycles. The injection will be given by manual push over 3 to 5 minutes in the abdominal SC tissues in left/right locations, alternating between individual doses. Dexamethasone will be dosed at 40 mg PO per week for subjects < 75 years and 20 mg PO per week for subjects ≥ 75 years during Cycles 1-4. Dose modifications will be mandated based on aggressive schedule of dose modification for toxicities as per specific guidelines. Otherwise, patients will continue at their best tolerated dose of lenalidomide on Days 1-21 and their best tolerated dose of carfilzomib on Days 1, 2, 8, 9, 15, 16 in Cycles 1-4 and Days 1, 2, 15, 16 in Cycles 5-8.

All subjects will have monthly clinic visits for disease assessments. Treatment will continue on protocol for up to 24 months or if carfilzomib, lenalidomide and daratumumab are permanently discontinued. If dexamethasone is discontinued due to toxicity, carfilzomib, lenalidomide and daratumumab may be continued if tolerated without dexamethasone. Toxicity will be graded using the National Cancer Institute Common Terminology Criteria for Adverse Events version 4. Patients who complete 24 cycles will then continue single-agent lenalidomide at best tolerated dose (up to 25 mg) in 28-day cycles. This regimen will continue until there is progression of the disease or the toxicities require discontinuation of the drug.

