##### **4.1.2.2 Treatment Phase**

Treatment will be continued until progression of disease according to IMWG criteria, unacceptable toxicities occur in individual subjects or consent is withdrawn. Cycles 1 through 4 are considered D-KRd induction cycles, Cycle 5-8 D-KRd consolidation, and Cycles 9-24 D-KRd maintenance cycles. After Cycle 4, subjects who are deemed candidates for ASCT will proceed to stem cell harvest as per institutional guidelines. However, the study design recommends a “delayed” transplant for ASCT candidates, as in subject having completed frontline KRd study without or with delayed transplant. This means that patients who are transplant candidates enrolled in this study will not proceed to ASCT; rather, they will have cells frozen down for a potential future transplant at progression or unacceptable toxicity after Cycle 4. After completion of stem cell harvest, patients will resume protocol treatment.

In the event that a subject’s risk status is unknown at the time of study entry, the subject will be required to re-consent to continue participation in this study if it is later determined that the subject has high-risk disease status and therefore may benefit from ASCT.

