## **8.2 Adverse Event Reporting Procedures**

Information about all AEs, whether volunteered by the subject, discovered by the treating investigator questioning, or detected through physical examination, laboratory tests or other means, will be collected and recorded in eVelos and followed as appropriate.

All adverse events **must** be reported in routine study data submissions to the Lead PI who will review and will be responsible for alerting all participating sites about the AE as required. **AEs reported using the Serious Event Reporting Form and/or MedWatch Form discussed below must also be reported in routine study data submissions in eVelos.** Details of the event must include severity, relationship to study drug, duration, action taken, and outcome as shown on the eCRF in eVelos. All AEs must be followed to resolution or stabilization regardless of relationship to study drug.

All AEs that are considered related to study regimen must be followed to resolution or stabilization if improvement is not expected.

AEs must be reported from the date the subject signs consent through 30 days post-last dose of study treatment or initiation of a new anticancer therapy, whichever occurs first. If a subject is enrolled but discontinues study prior to receiving any study drug, only SAEs that are considered related to study procedures must be reported through the end-of-study visit. AEs that completely resolve and then recur should be recorded as a new AE. For subjects who complete the end of study visit less than 30 days following their last dose of study drug, a follow up of ongoing AEs should be attempted by telephone, and documented in the subject's source. AEs continuing at 30 days post-last dose should have a comment in the source by the treating investigator that the event has stabilized or is not expected to improve. SAEs continuing at 30 days post-last dose should be followed until resolution or stabilization.

The treating investigator is responsible for evaluating all AEs for relationship to study drug and for seriousness, obtaining supporting documents, and determining that documentation of the event is adequate. Adverse events will be assigned a severity grade using the NCI-CTCAE grading scale v4.0. The

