### **13.6.2 DSMB Member Scope of Work**

The Data and Safety Monitoring Board is an independent body composed of two medical oncologists and a biostatistician. Their main responsibilities are to review data and safety monitoring reports prepared by the Coordinating Center at periodic intervals. They will also monitor patient accrual, submit requests for additional analyses as deemed necessary, evaluate the performance of the participating clinical sites, evaluate the performance of the Coordinating Center, and provide recommendations to the steering committee regarding protocol modifications and whether the study should continue as planned. This DSMB will be provided with the toxicity data from the completed and published KRd trial (Jakubowiak et al, Blood 2012;120:1801-9), and they will review reports of adverse events to ensure patient safety as well as efficacy analyses to determine whether sufficient evidence has emerged that toxicity in the D-KRd trial exceeds historical toxicity in the KRd trial, which would prompt consideration of early termination of the trial. The DSMB will participate in conference calls and/or face-to-face meetings with the Lead Principal investigator and study statisticians approximately every six months. The DSMB may also call for additional meetings and data reviews if they feel it is necessary for the safety of patients or the progress of the study. The DSMB is expected to approve meeting minutes and maintain confidentiality of all study results.

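### Section 10.2.3 compares worst toxicity grade per patient between 24 planned cycles of D-KRd and 18 cycles of historical KRd+ASCT with no common window, so regimen effect and length of observation are mixed

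*Protocol*

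**What the plan says.** Section 10.2.3 states that "safety of the regimens will be assessed by comparing CTCAE Grade toxicity occurrence between D+KRd and historical KRd+ASCT data". The measure is then set out: "The maximum graded toxicity overall and within SOC will be reported per patient with the results summarized by treatment group and frequencies compared". The tests on those frequencies are chi-square, or Fisher's exact where that is the better choice. No window, cycle range or exposure adjustment is attached. In the same section the MRD rate and the improvement in response are tied to stated months.

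The collection rule for adverse events is in Section 8.2: "AEs must be reported from the date the subject signs consent through 30 days post-last dose of study treatment", or to new anticancer therapy if that comes first. With no other window given, a patient's worst grade is therefore the worst over the whole treatment course.

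The planned courses differ in length. For D-KRd, Section 4.1.2.2 gives "Cycle 5-8 D-KRd consolidation, and Cycles 9-24 D-KRd maintenance cycles", and Section 4.1 adds that "Patients who complete 24 cycles will then continue single-agent lenalidomide at best tolerated dose". For KRd+ASCT, Section 1.7 describes "candidates with 4 KRd cycles before ASCT followed by 4 cycles of KRd consolidation, followed by 10 cycles of KRd maintenance" and gives the total as 18 cycles.

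Section 13.6.2 uses a different historical trial. The DSMB receives toxicity data from a completed, published KRd trial and judges "whether sufficient evidence has emerged that toxicity in the D-KRd trial exceeds historical toxicity in the KRd trial". An excess would prompt consideration of early termination.

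**The concern.** The proportion of patients whose worst grade reaches a given level cannot fall as observation lengthens. If one group is watched for six more cycles, a test on those proportions compares the regimens and the lengths of observation together, and no result can separate the two. The protocol recognises this elsewhere: Section 1.7 puts the slightly higher toxicity in the daratumumab arm of a cited randomised trial down largely to longer time on treatment.

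Safety and tolerability is a named secondary objective (Section 2.2). At stake is whether a difference from KRd+ASCT, or the lack of one, can be read as a property of the regimen. The primary endpoint is not affected.

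**Working it through.** **Inputs from the protocol.** Historical KRd+ASCT: 4 + 4 + 10 = 18 cycles, which reproduces the total stated in Section 1.7. D-KRd: 24 cycles (Sections 4.1 and 4.1.2.2). Ratio 24/18 = 1.33. D-KRd sample size: 45 (Section 10.2.1). Both cycle counts are planned maxima. Appendix 8 (the adverse-event footnote) ends recording 30 days after the last D-KRd dose, so I take 24 cycles as the D-KRd window and leave later lenalidomide out.

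**Inputs assumed.** The protocol gives no significance level for this test and no historical sample size. I use two-sided 5% and 53 to 100 historical patients. All patients are taken to complete the planned cycles.

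**Step 1: equal and constant per-cycle risk.** If a proportion p has the event within 18 cycles, the proportion within 24 is 1 − (1 − p)^(24/18).

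- p = 10%: 1 − 0.90^1.333 = 13.1%, a gap of 3.1 points.
- p = 30%: 1 − 0.70^1.333 = 37.8%, a gap of 7.8 points.
- p = 50%: 1 − 0.50^1.333 = 60.3%, a gap of 10.3 points.

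**Step 2: the same 30% event with risk clustered early.** The cumulative hazard over 18 cycles is H = −ln(0.70) = 0.3567. Put a share a of H in the first k cycles and spread the rest evenly over cycles k+1 to 18, continuing at that rate to cycle 24. The 24-cycle hazard is H × [1 + 6(1 − a)/(18 − k)], and the proportion is 1 − exp(−hazard).

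- a = 0.5, k = 4: 0.3567 × 1.2143 = 0.4331, giving 35.2%.
- a = 0.8, k = 8: 0.3567 × 1.12 = 0.3995, giving 32.9%.
- a = 0.8, k = 4: 0.3567 × 1.0857 = 0.3872, giving 32.1%.

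**Step 3: how often the test rejects when per-cycle risk is the same.** Exact Fisher rejection probability, 45 against 75 patients:

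| 18-cycle rate | 24-cycle rate | Risk pattern | Rejection |
|---|---|---|---|
| 30% | 30% | equal windows | 4.0% |
| 30% | 37.8% | constant | 12.4% |
| 30% | 35.2% | half in Cycles 1-4 | 7.6% |
| 30% | 32.9% | 80% in Cycles 1-8 | 5.2% |
| 30% | 32.1% | 80% in Cycles 1-4 | 4.6% |
| 50% | 50% | equal windows | 3.7% |
| 50% | 60.3% | constant | 16.2% |

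With the chi-square test and 53 to 100 historical patients, the constant-risk figures are about 13-16% (30% event) and 18-21% (50% event), against about 5% with equal windows. None of these calculations includes transplant toxicity.

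**Step 4: exposure at a DSMB review.** Reviews come about every 6 months (Section 13.6.1) and accrual takes 12-18 months (Section 6). With uniform accrual, the longest exposure at 6 months is 6 × 30.4375/28 = 6.5 cycles and the mean is half that, 3.3. At 12 months the mean is 6.5 cycles. Take a 30% event over an assumed 18-cycle reference and a doubled D-KRd hazard. The observed proportion is then 11.9% at 6 months and 21.9% at 12 months under constant risk. With half the hazard in Cycles 1-4 it is 22.2% and 30.9%. A crude comparison would be sensitive to exposure, but by an amount that depends on the risk pattern and on the reference length, which the protocol does not give.

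**The case against.** **This is detail for the analysis plan.** Adverse-event windows are often left there, and the whole-course reading is an inference from Section 8.2. That is fair as far as it goes. But Section 10.2.3 does fix the comparator, the measure and the test. Carried out as written, those choices confound toxicity with exposure.

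**Transplant toxicity works the other way.** The comparator includes high-dose therapy with transplant between Cycles 4 and 5, and a worst-grade measure would capture its acute effects. This stands. A reader might infer that the final analysis will show a D-KRd excess produced only by longer observation. The documents do not support that: exposure pushes one way, transplant the other, and neither can be sized against the other from the text. The calendar gap is also not simply 672 against 504 days, since the transplant interval is not in the cycle count.

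**Constant risk is doubtful.** This also stands. Section 1.6.1 places infusion reactions mainly at the first full infusion, Sections 6.7.1 and 6.7.3 place first-dose effects and tumour lysis in Cycles 1-2, and carfilzomib and daratumumab are given less often from Cycle 9. With early clustering, rejection falls to about 5-8%. The exposure bias shrinks without disappearing.

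**The DSMB is not bound to a crude comparison.** A reader might infer that the interim reviews will hide a real excess. Section 13.6.2 prescribes no statistic, the board includes a biostatistician and may request analyses, and the length of the KRd trial is not stated. Section 6.6 separately provides for stopping for review after a related Grade 5 toxicity, or after Grade 4 non-hematologic toxicity in two or more patients. Those provisions do not depend on historical rates. The stronger reading fails; only the modest point that nothing requires matched exposure survives.

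**Conclusion.** The point holds for Section 10.2.3. A worst-grade-per-patient comparison of 24 planned cycles with 18, without a common window, cannot separate regimen from length of observation. The exposure component favours an apparent D-KRd excess: for a 30% event, about 8 points under constant per-cycle risk and about 2 to 5 points if risk clusters early. False rejection of 12-16% (Fisher, 75 historical patients) applies only under constant risk, and is about 5-8% for the 30% event under clustering. These sizes assume full completion of planned cycles and an unstated historical sample size. The net direction, once transplant toxicity is included, is unknown. For Section 13.6.2 this is an improvement worth making, not an error in the text.

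**What to change.** In Section 10.2.3:

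- Make the formal toxicity comparison over a common window, for example worst grade among events with onset in Cycles 1-18, with Cycles 1-8 as support. At equal per-cycle risk and without transplant effects, rejection then returns to about 4% (Fisher) or 5% (chi-square).
- State that transplant-period events count as part of the KRd+ASCT regimen, and also show results without them. The Cycles 1-8 window spans the transplant too, so the rule is needed for both.
- Add incidence per patient-cycle at risk, computed within the same window. Over unequal lengths, a rate averaged across declining risk would favour the longer course.
- Report Cycles 19-24 descriptively, without a historical comparison.

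In Section 13.6.2, as a secondary change, provide the DSMB with historical KRd toxicity by cycle so that partly exposed D-KRd patients are compared at matched exposure. The provisions in Section 6.6 stay as they are.

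The cost is wording in two sections, cycle of onset derived in the trial data and in the historical data where available, and fewer late events in the formal test. Section 10.2.1 refers to the team's own prior KRd studies, so onset dates may be at hand, but the protocol does not establish this. If they are not, the comparison should be descriptive, with the difference in planned exposure stated beside it. Treatment, visits and sample size do not change.
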